### Interventions

The participants randomly assigned to the usual care (control) group will receive general advices from primary care centre medical staff about the positive effects of physical activity. The researchers will give 4 conferences (1 per month) explaining the benefits of exercise for longevity, prevention and treatment of diseases, the benefits of the Mediterranean diet, nutritional education, ergonomic advises, exercise to perform at home (e.g. stretching, strength training) and strategies to increase their daily physical activity levels.

The exercise intervention will be performed in four groups so that each group will comprise 15–20 participants. The groups will train 3 days/week (60 min per session) for a 16-week period at the primary care centre of Granada. The exercise intervention will meet the training standards of the American College of Sports Medicine [17] for adults. The exercise sessions will be designed, carefully supervised, guided and instructed by qualified exercise professionals.

Each exercise session will include a 10 min warm-up period with walks and mobility exercises, followed by 40 min of a main part which will vary across week days (i.e. 3 different models of session). Sessions will finish with a 10 min cool-down period of stretching and relaxation exercises. The three model sessions will be: (i) First session of the week will involve circuit training including resistance exercises in a stepped progression during the program. Resistance circuit training will include 2–3 set of 6–10 exercises. The participants will perform 10–20 repetitions of multi-joint exercises and/or single joint exercises targeting major muscle groups such as biceps curls, triceps extensions, arm side lifts, shoulder elevations, chest press, lateral leg elevations, stands up from seated position, lunge, sideways lunge and step-up/step-down, squads, lower back extensions, abdominal crunch/curl-up and calf raises among others. Participants will carry out bodyweight exercises at the beginning of the program and, if it is necessary, free weights (0.5–3 kg barbells) and resistance bands will be used to reach the optimal intensity. The load will be gradually increased and each participant will individualize her effort to reach the intensity designed for each session; (ii) Second session of the week will include balance-oriented activities (position changes, monopodal and bipodal stances, backwards walks, …) and dancing (aerobic exercises); (iii) Third session of the week will combine aerobic, resistance strength and coordination exercises.

Heart rate will be measured with heart rate monitors (Polar Electro OY, Finland) to control the intensity of the sessions. One third of the participants in the intervention group will wear heart rate monitors in 1/3 of the sessions, both randomly selected. We will monitor the ratings of perceived exertion (RPE) using the Borg 6-20 RPE scale [18] during all the sessions. Intensity (expressed as RPE) will be expected to range from 12 to 16. The exercise volume and intensity programmed is shown in Table 2.

**Table 2 Tab2:** Exercise intervention

Sesion structure	Content								
Warm-up 10’ minutes	Joint mobility and different walk modalities								
Conditioning 40 min	Week	1-2	3-4	5-6	7-8	9-10	11-12	13-14	15-16
	Intensity RPE	12-13	12-13	13-14	13-14	14-15	14-15	15-16	15-16
	Monday								
	Resistance training circuit*	6 exercises	8 exercises	8 exercises	8 exercises	8 exercises	8 exercises	10 exercises	10 exercises
	Set x repetitions	2 × 15	3 × 15	3 × 18	3 × 20	3 × 18	3 × 15	3 × 12	3 × 10
	Wednesday	Choreographies and aerobic exercises							
	Friday	5 exercises	6 exercises	6 exercises	6 exercises	7 exercises	7 exercises	8 exercises	8 exercises
	Resistance exercises (RE)^a^ and aerobic exercises (AE)^b^	2RE + 1AE + 2RE	3RE + 1AE + 2RE	3RE + 1AE+ 2RE	3RE + 1AE+ 2RE	2RE + 1AE + 2RE +1AE + 1RE	2RE + 1AE+ 2RE + 1AE + 1RE	2RE + 1AE + 2RE +1AE +2RE	2RE +1AE + 2RE +1AE + 2RE
Cool-down 10 min	Stretching and relaxation exercises								

RPE, rating of perceived exertion; *The circuit is composed of trunk, upper and lower extremities exercises. Body-weight, free weights (0.5–3 kg barbells) and resistance bands exercises. The load will be gradually and individualized increased for each participant to reach the intensity designed for each session; ^a^The set and repetitions in resistance exercise will be the same than the resistance circuit training;^b^ The aerobic exercise will have a duration between 2–4 min

To maximize adherence, several strategies will be implemented including music in all sessions, individualized attention during the intervention sessions, and telephone calls following non-attendance. The researchers will control and register the presence of adverse event during and between classes.

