### Randomization and blinding

After baseline assessments, all participants will be randomized to either exercise intervention or control (non-exercise) group. A computer generated simple randomization sequence will be created before participants will be enrolled, to allocate participants to either the exercise intervention or control group (1:1). The randomization sequence will be prepared by a member of the research team with no clinical involvement in the trial. The allocation will be concealed in a password protected computer file. Whereas the participants will be aware of their group allocation, outcome assessors and data analysts will be blinded to the allocation.

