### Secondary outcomes

#### Socio-demographic and clinical information

Demographic and other health information will be collected using a questionnaire. This anamnesis will include questions regarding smoking and alcohol habits, history of illness (as osteoporosis, CVD, hypertension, diabetes), menopause status, indicators of socio-economic status (such as personal and household income, education level…), marital status, and number of children. The pharmacology register as well as the number and reason of medical visits will be consulted by the primary care medical staff in collaboration with members of the research team through the medical database.

Systolic and diastolic blood pressure, as well as resting heart rate, will be measured after 5 min of rest, on 2 separate occasions (with 2 min between trials), with the person seated (Omron Health Care Europe B.V. Hoolddorp). The lowest value of the two trials will be selected for the analysis.

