#### Quality of life, mental health and positive health

We will determine participants’ quality of life with the *Short-Form Health Survey 36* (SF-36) [33]. The SF-36 is a generic instrument for assessing health-related quality of life. It contains 36 items grouped into 8 dimensions: physical functioning, physical role, body pain, general health, vitality, social functioning, emotional role, and mental health. The scores range from 0 to 100 in every dimension, where higher scores indicate better health.

The *EQ-5D-5 L* consists of two parts. The first will be used to assess 5 dimensions of health related quality of life: mobility, self-care, usual activities, pain/discomfort and anxiety/depression, each of which is defined through five severity levels [34, 35]. The instrument therefore defines 3125 different health states from all the possible combinations of dimensions and levels of severity. EQ-5D-5 L health states may be converted into a single index value [34, 35]. This index ranges from 1 (best health status) to 0 (death). The second part consists of a 20-cm, vertical visual analogue scale (VAS), in the form of a thermometer, with endpoints of worst and best imaginable health status (scored 0 and 100, respectively) [34, 35]. This questionnaire will be administered at 3 different time points: at the beginning of the study, at 8 weeks and at 16 weeks, moreover it will be used to perform the cost-utility analysis.

The *Rosenberg Self-Esteem Scale* [36] is a 10-item scale to analyse the global self-esteem [37]. Each item is rated on a 4-point Likert scale, ranging from 1 = “strongly disagree” to 4 = “strongly agree”. The score ranges from 10 to 40, and higher scores reflect greater self-esteem.

The *brief COPE* [38, 39] is a 28-item scale that assesses coping strategies. Participants will be asked to rate how often they use specific coping strategies on a 4-point Likert scale, from 0 = “I haven’t been doing this at all” to 3 = “I’ve been doing this a lot”. The 28 items are paired together describing 14 different coping strategies: active coping, planning, positive reframing, acceptance, humour, religion, use of emotional support, use of instrumental support, self-distraction, denial, venting, substance use, behavioural disengagement and self-blame. Score for each subscale ranges from 0 to 6, and higher score indicates more frequency of the particular coping strategy.

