#### Cost-effectiveness analysis

A cost-utility analysis with a health system perspective will be conducted in line with the methodological recommendations suggested by Lopez-Bastida et al. [60], and the guidelines defined in the economic evaluation literature [19, 61].

The study will be conducted considering the costs and the health effects of the intervention. Only direct costs of the program will be identified and valued. As direct costs for both groups, the drugs consumption, primary care visits, and hospital admissions will be considered. In the intervention group, the time dedicated by sport professionals of the exercise program will also be considered. Their total remuneration will be calculated based on the collective agreement for these professionals. First, for each group (intervention and control) an average of cost and effectiveness (the mean QALYs gained) will be calculated. Secondly, the ICER [19] will be calculated. To analyse the uncertainty in model parameters and verify the robustness of the ICER, various deterministic and probabilistic sensitivity analyses will be held [62]. The probabilistic analysis will be carried out through bootstrapping non parametric methods with 1000 replications. The resulting 1000 ICER replications will be plotted on the cost-effectiveness plane and will be used to construct an acceptability curve [63]. The cost-effectiveness plane is a graphical way of presenting cost-effectiveness results, with the difference in costs on the vertical axis and the difference in health benefits on the horizontal axis. Since incremental costs and health benefits can both be either positive or negative, there are four possible combinations, which will be reflected in the four quadrants of the cost-effectiveness plane:Upper-left quadrant: intervention less effective and more costly than comparator.Lower-left quadrant: intervention less effective and less costly than comparator.Upper-right quadrant: intervention more effective and more costly than comparator.Lower-right quadrant: intervention more effective and less costly than comparator.

The acceptability curve represents the proportion of simulations in which the intervention was considered cost-effective over a range of values of the threshold cost- per-QALY [64]. All analyses will be conducted in Stata v.13 (Stata Corp, College Station, TX, USA).

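### The only stated adverse-event procedure follows the exercise classes, so registered events, especially minor ones, would be ascertained unequally and could not be fairly compared between arms

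*Protocol article*

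**What the plan says.** The Interventions section of the protocol article ends its account of the exercise programme, just after the adherence measures, with: "The researchers will control and register the presence of adverse event during and between classes". No other sentence in the article describes how adverse events are collected.

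The same section sets out the contact in each arm. For exercise: "The groups will train 3 days/week (60 min per session) for a 16-week period at the primary care centre of Granada". Missed sessions bring further contact, since the adherence measures include "individualized attention during the intervention sessions, and telephone calls following non-attendance". For controls, besides general advice from medical staff: "The researchers will give 4 conferences (1 per month) explaining the benefits of exercise for longevity". Those conferences also cover exercise to do at home, including strength training.

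Two other sections describe health-event data that are not limited to one arm. Under Socio-demographic and clinical information: "The pharmacology register as well as the number and reason of medical visits will be consulted by the primary care medical staff". Under Cost-effectiveness analysis: "As direct costs for both groups, the drugs consumption, primary care visits, and hospital admissions will be considered".

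Adverse events are not listed among the primary or secondary outcomes, and the Statistical analysis section plans no comparison of them.

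**The concern.** Registering events during a supervised class is ordinary oversight of the session. Extending registration to the time between classes changes what is collected. It then covers general health events over the whole 16 weeks, such as falls, joint and muscle complaints and passing illness. These also occur in women who do not attend classes. Without a control rate gathered in the same way, an event between classes cannot be attributed to exercise or cleared of it.

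What is at stake is any safety statement the trial makes. The Discussion section calls exercise safe and argues that its prescription in primary care should be encouraged, so readers will look to this trial for harms as well as benefits. A raw comparison of registered events would lean towards an apparent excess in the exercise arm, even if the true risks were equal. Controls who take up the home exercise they are taught also have some exposure, and no matching registration is stated for them.

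**Working it through.** **Step 1. Contacts to which registration could attach.**

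- Exercise arm: 3 sessions per week × 16 weeks = 48 scheduled classes, plus calls after missed sessions (Interventions).
- Control arm: 4 monthly conferences (Interventions), with no recording duty stated.
- Ratio of scheduled programme contacts: 48 / 4 = 12.

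This ratio describes opportunity only. The article does not say that women are questioned at each class, so 12 to 1 is not a measure of bias.

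**Step 2. Which events have a source in both arms.**

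| Type of event | Exercise arm | Control arm |
|---|---|---|
| Hospital admission | class-tied register; cost data | cost data |
| Primary care visit and its reason | class-tied register; medical database; cost data | medical database; cost data |
| Event leading to a drug record | class-tied register; pharmacology register | pharmacology register |
| Minor event with no visit or drug record | class-tied register | no event source stated |

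The asymmetry is complete only in the last row. In the others a symmetric source exists, though it is collected as clinical or cost information and is not designated as safety data.

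**Step 3. How much unequal capture could matter.** The article gives no adverse-event rate and plans no test, so this is an illustration. The 75 women per arm come from the Sample size section. The assumptions are:

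- the same true risk p in both arms;
- full capture in the exercise arm;
- a captured fraction c in controls.

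Expected recorded events are 75 × p in the exercise arm and 75 × p × c in controls. For p = 0.20 and c = 0.25, that is 75 × 0.20 = 15 against 75 × 0.20 × 0.25 = 3.75.

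The last column is the probability that a two-sided Fisher exact test at 0.05 shows an excess in the exercise arm. It sums over the two independent binomial distributions.

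| p | c | Expected, exercise | Expected, control | Chance of a falsely significant excess |
|---|---|---|---|---|
| 0.10 | 0 | 7.5 | 0 | 77% |
| 0.10 | 0.25 | 7.5 | 1.9 | 34% |
| 0.10 | 0.50 | 7.5 | 3.8 | 13% |
| 0.20 | 0 | 15 | 0 | above 99% |
| 0.20 | 0.25 | 15 | 3.8 | 76% |
| 0.20 | 0.50 | 15 | 7.5 | 32% |
| 0.30 | 0 | 22.5 | 0 | above 99% |
| 0.30 | 0.25 | 22.5 | 5.6 | 94% |
| 0.30 | 0.50 | 22.5 | 11.3 | 53% |

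With equal capture (c = 1) the same calculation gives 1% to 2% at each risk.

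**Step 4. Reach into the planned analyses.** The incremental cost-effectiveness ratio uses costs and QALYs. The secondary outcomes are clinical measurements, fitness tests and questionnaires. None uses the adverse-event register.

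**The case against.** The strongest case on the other side has four parts.

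1. **Condensed article.** The sentence does not say that events are registered only around classes, and it does not exclude controls. It reads as supervision of the programme, and control-arm procedures may sit in the full protocol. This stands as a limit: that controls are never asked about events is something a reader might infer, but the article does not say so. It does not remove the point. The article states an ascertainment rule and ties it to a schedule that one arm has, so following the rule as written yields unequal registration.

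2. **Symmetric data exist.** A reader might conclude that the arms cannot be compared for safety at all, or that no control count could be formed. The documents do not support that. Visit reasons, drugs and admissions allow counts and risk differences for medically attended events. Pain is also scored by the EQ-5D-5L, the SF-36 and the Blatt-Kupperman index, none of them limited to one arm. This objection stands for attended events. The pain scores help less, because they measure status on a scale and do not record events. Minor unattended events remain one-sided.

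3. **A count of 48 against 0.** This is tempting but unsupported. It treats each class as a question asked and ignores the conferences and questionnaire contacts in the control arm.

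4. **No planned comparison.** Adverse events are not an outcome, and a descriptive exercise-arm list is interpretable by itself. This stands too. The harm arises only if registered events are set against the control arm or used to support a claim of relative safety.

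**Conclusion.** The point holds in a limited form. The one stated procedure follows a schedule that only the exercise arm has, so events registered under it would be ascertained unequally and could not be fairly compared between arms. The problem is greatest for minor events that bring no medical visit. A limited comparison of medically attended events remains possible, and the primary analysis is untouched.

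The size cannot be fixed from the article. Under the assumed risks of 10% to 30%, and capture in controls of a quarter to a half of that in the exercise arm, the chance of a spurious significant excess ranges from 13% to 94%. These figures rest on equal true risks, full capture in the exercise arm and a test that the plan does not propose. They show that partial under-capture is enough to mislead; they do not predict this trial's result. The conclusion also assumes that no fuller document prescribes matching registration in controls.

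This should be corrected, but it does not threaten the trial's main result.

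**What to change.** The EQ-5D-5L already provides suitable contacts: "This questionnaire will be administered at 3 different time points: at the beginning of the study, at 8 weeks and at 16 weeks". Three changes follow.

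- At 8 and 16 weeks, put the same structured adverse-event question to both arms, with the same definition and recall window.
- Base any between-arm safety statement on those answers, together with the visits and admissions taken from records for both groups.
- List class-registered events separately, as descriptive information on the exercise arm, and do not set them against control counts.

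The cost is one added item at two existing administrations and some staff time to classify the answers. The article does not say how the 8-week questionnaire is delivered, so that should be settled when the item is added. No outcome and no sample size changes.

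The downsides are a small participant burden, recall over about eight weeks (16 − 8), and self-report by women who know their allocation. On the last, the Randomization and blinding section is explicit: "Whereas the participants will be aware of their group allocation, outcome assessors and data analysts will be blinded to the allocation". Exercise participants may report more readily, so identical questions reduce unequal ascertainment without removing it. The record-based events are a useful check for that reason.

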### Primary and secondary outcomes

#### Primary outcomes

The Incremental Cost Effectiveness Ratio (ICER) [19]. For each group (intervention and control) an average of cost and health effects will be calculated. The measurement of health effects is defined as the Quality Adjusted Life Years (QALYs). The QALYs are calculated multiplying the years of life by the participants’ quality of life. The participants’ quality of life will be assessed by the EQ-5D-5 L questionnaire. The ICER will be calculated dividing the difference between the average costs of both groups by the difference in mean QALYs gained in both groups [19].$$ \mathrm{ICER}=\frac{\mathrm{Cos}{\mathrm{t}}_{\mathrm{Intervention}}-\mathrm{C}\mathrm{o}\mathrm{s}{\mathrm{t}}_{\mathrm{Control}}}{\mathrm{QAL}{\mathrm{Y}}_{\mathrm{Intervention}}-\mathrm{Q}\mathrm{A}\mathrm{L}{\mathrm{Y}}_{\mathrm{Control}}} $$

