### Sample size

The number of participants to be included in the study was calculated on the basis of the change in quality of life as assessed with the *EuroQol 5D (*EQ-5D-5 L). To the best of our knowledge, there is no available data regarding group differences in changes in quality of life following any type of intervention in middle aged women. Therefore, we assumed a difference of 0.07 units as clinically meaningful based on previous observations from our group (unpublished observations). Therefore, a total of 124 participants (62 per group) is needed to detect a mean group difference of 0.07 and a standard deviation of 0.12 in the total EQ-5D score with a power of 90 % and α of 0.05. However, we will attempt to exceed this sample size to allow for withdrawals. Assuming a maximum lost-to-follow up of 20 %, a minimum of 75 participants per group will be recruited (*n* = 150).

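### The primary ICER is built from raw group means, so the baseline adjustment promised for the primary outcome never reaches its QALY difference

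*Protocol article*

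**What the plan says.** Four places in the protocol article bear on the point.

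- **Primary outcomes.** The ICER is obtained by "dividing the difference between the average costs of both groups by the difference in mean QALYs gained in both groups". The displayed formula is the same ratio of differences and has no covariates. On the QALY itself: "The QALYs are calculated multiplying the years of life by the" woman's quality of life, measured by EQ-5D-5L.
- **Cost-effectiveness analysis.** The order of steps is repeated. For each group "an average of cost and effectiveness (the mean QALYs gained) will be calculated", the ICER is then formed, and a non-parametric bootstrap with 1000 replications supplies the cost-effectiveness plane and acceptability curve. Baseline utility is not mentioned.
- **Statistical analysis.** Effects on the primary as well as the secondary outcomes are to be examined by a covariance model for repeated measurements, with age and the baseline value as covariates.
- **Quality of life, mental health and positive health.** EQ-5D-5L is given "at the beginning of the study, at 8 weeks and at 16 weeks", and the same sentence assigns it to the cost-utility analysis.

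**The concern.** The sections do not fit together. The covariance model needs one value per woman per visit. The ICER is a single number for the whole trial, with no participant-level value and no baseline value. The promised adjustment therefore cannot be applied to the primary outcome as defined, and the section that does compute the ICER does not carry the adjustment into the QALY difference.

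This matters because the baseline index is itself part of a QALY accumulated over 16 weeks, and it predicts the later values. Allocation is by simple randomization, with no stated balancing on EQ-5D. Any chance difference at baseline therefore passes into the denominator of the ICER, and that denominator is expected to be only about 0.01 QALY. The bootstrap shows the sampling spread, but it resamples around the observed raw difference. An observed imbalance stays in the point estimate, in the centre of the plane and in the acceptability curve.

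**Working it through.** **Inputs from the article (Sample size).** The difference to detect is 0.07, the significance level 0.05 and the power 90 %. The spread is given as "a standard deviation of 0.12 in the total EQ-5D score". These lead to 62 per group before dropout, and 75 per group are to be recruited. The horizon is 16/52 = 0.3077 year.

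**Assumptions (not in the article).** SD 0.12 at each visit; the same correlation r between any two visits, 0.5 to 0.7; a linear gain reaching 0.07 at week 16; no further gain in precision from age.

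**1. The article's own figure.** n = 2(1.960 + 1.282)² × 0.12²/0.07² = 61.8, so 62 per group two-sided. The stated number is reproduced.

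**2. Effect on the QALY scale.** With u0, u8 and u16 the index at the three visits, the area under the curve is Q = (16/52)(0.25·u0 + 0.5·u8 + 0.25·u16). A linear gain gives (16/52)(0.5 × 0.035 + 0.25 × 0.07) = 0.0108 QALY.

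**3. Chance imbalance.** The SE of the baseline difference is 0.12·√(2/75) = 0.0196. A baseline difference d shifts the expected later differences by r·d, so the raw QALY difference moves by (16/52)(0.25 + 0.75r)·d.

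| r | shift at 1 SE | % of 0.0108 | % at 1.96 SE |
|---|---|---|---|
| 0.5 | 0.0038 | 35 | 69 |
| 0.6 | 0.0042 | 39 | 77 |
| 0.7 | 0.0047 | 43 | 85 |

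**4. Precision at 75 per group.** The variance of each estimator is (16/52)² × 0.12² × (2/75) × k, where

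- raw means: k = 0.375 + 0.625r
- adjusted for baseline: k = 0.375 + 0.625r − (0.25 + 0.75r)²
- change from baseline, Q − (16/52)·u0: k = 0.875(1 − r)

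| r | SE raw | SE change | SE adjusted | variance, adjusted/raw |
|---|---|---|---|---|
| 0.5 | 0.0050 | 0.0040 | 0.0033 | 0.43 |
| 0.6 | 0.0052 | 0.0036 | 0.0031 | 0.35 |
| 0.7 | 0.0054 | 0.0031 | 0.0028 | 0.26 |

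Under change from baseline, the carry-over of a one-SE imbalance is −(16/52) × 0.75(1 − r) × 0.0196. That is −0.0023, −0.0018 and −0.0014 for r = 0.5, 0.6 and 0.7, or 21 to 13 % of the effect in the opposite direction.

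**5. What this means in practice.** At r = 0.6 and a true effect of 0.0108, the chance that the denominator has the wrong sign is Φ(−0.0108/0.0052), about 2.0 %, for raw means and below 0.1 % after adjustment. As a gauge of precision only, since the ICER is not itself tested, power for the QALY difference at 62 per group is Φ(effect/SE − 1.96). Over r = 0.5 to 0.7 this is about 50 to 44 % for raw means, 69 to 89 % for change from baseline and 85 to 94 % adjusted.

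**6. Sensitivity.**

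- *SD.* The Sample size section speaks of change in quality of life, so 0.12 may be the SD of change. The per-visit SD would then be 0.12/√(2(1 − r)), which is 0.120, 0.134 and 0.155 for r = 0.5, 0.6 and 0.7, and the one-SE shift becomes 35, 44 and 56 % of the effect. The variance ratios in step 4 do not depend on the SD.
- *Shape of the gain.* If the full 0.07 is present by week 8, the effect is 0.0162 QALY and the shift at r = 0.6 is 26 % of it. If the gain comes only after week 8, the effect is 0.0054 QALY and the shift is 78 %.

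**The case against.** The strongest reply is that this concerns precision and not validity. Allocation is random and 1:1, so the raw difference is unbiased, and chance imbalance is part of the variation that the planned bootstrap displays. That stands. The loss is in efficiency and in the estimate conditional on the imbalance actually observed.

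A second reply is that the article does promise baseline adjustment for the primary outcome, so it would be wrong to say that the plan ignores it. That also stands. The fault is that the promise is attached to a model that cannot deliver it for a ratio of group means.

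A third is that the word *gained* may mean change from baseline. The text allows that reading. It removes most of the carry-over and reverses the rest, but at r = 0.6 it still leaves an SE of 0.0036 against 0.0031 with adjustment.

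A fourth is that regression details belong in an analysis plan that is not shown. This holds for model detail, but the article itself fixes the estimator in words, as a formula and as an order of steps, without the adjustment.

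Four stronger readings are tempting, and the article does not support them:

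- *Imbalance dominates the result or sets its sign.* At SD 0.12 and r = 0.6, a wrong-sign denominator is about a 2 % event.
- *The plan credits the full gain from day one.* Multiplying a week-16 gain of 0.07 by 16/52 would give 0.0215 QALY, twice the linear figure. But no section says to do this, and all three EQ-5D visits are assigned to the cost-utility analysis. Only the rule for combining them is left unsaid.
- *The cost difference is distorted to a comparable degree.* The article gives no figures from which this could be judged.
- *Adjustment for pre-trial costs is required.* The article does not say that such costs are collected.

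**Conclusion.** The point holds as a mismatch between sections with a real cost in precision. The primary ICER is defined on raw group means, and the age and baseline adjustment promised for the primary outcome does not reach it or its bootstrap. With SD 0.12 at each visit and correlation 0.5 to 0.7, a one-SE imbalance is worth about 35 to 43 % of a linear 0.0108 QALY effect, and the raw estimator has roughly 2.3 to 3.9 times the variance of the adjusted one (1/0.43 to 1/0.26). The correlation, the per-visit SD and the linear gain are assumptions. A change-from-baseline reading narrows the gap without closing it. The raw analysis is not biased, and the trial's conclusion is not invalidated. A large, nearly free gain in precision is left unused in the primary outcome.

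**What to change.** 1. In Primary outcomes, define each woman's QALYs as the area under her EQ-5D-5L index at weeks 0, 8 and 16 by the trapezoidal rule, and say whether *gained* means this total or a change from baseline.
2. Take the ICER denominator from a regression of QALYs on group, baseline EQ-5D index and age.
3. In Cost-effectiveness analysis, refit that regression in every bootstrap replicate, so that the plane and the acceptability curve use the adjusted difference.
4. Report the ICER from unadjusted means as a sensitivity analysis.
5. In Statistical analysis, restrict the repeated-measures covariance model to participant-level outcomes and refer to the new text for the ICER, so that the three sections agree.

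Adjusting incremental costs for pre-trial costs is optional, and only if those data can be obtained.

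The cost is a few sentences and a few lines of code. The EQ-5D visits are already scheduled, so no new data are needed. The wording should be settled before anyone sees outcome data by group.
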